## Abstract

**Background:**

In Spain, family is the main source of care for dependent people. Numerous studies suggest that providing informal (unpaid) care during a prolonged period of time results in a morbidity-generating burden. Caregivers constitute a high-risk group that experiences elevated stress levels, which reduce their quality of life.

Different strategies have been proposed to improve management of this phenomenon in order to minimize its impact, but definitive conclusions regarding their effectiveness are lacking.

**Methods/Design:**

A community clinical trial is proposed, with a 1-year follow-up period, that is multicentric, controlled, parallel, and with randomized allocation of clusters in 20 health care centers within the Community of Madrid. The study's objective is to evaluate the effectiveness of a standard care intervention in primary health care (intervention CuidaCare) to improve the quality of life of the caregivers, measured at 0, 6, and 12 months after the intervention.

One hundred and forty two subjects (71 from each group) ≥65 years, identified by the nurse as the main caregivers, and who provide consent to participate in the study will be included.

The main outcome variable will be perceived quality of life as measured by the Visual Analogue Scale (VAS) of EuroQol-5D (EQ-5D). The secondary outcome variables will be EQ-5D Dimensions, EQ-5D Index, nursing diagnosis, and Zarit's test. Prognostic variables will be recorded for the dependent patient and the caregiver.

The principle analysis will be done by comparing the average change in EQ-5D VAS value before and after intervention between the two groups. All statistical tests will be performed as intention-to-treat. Prognostic factors' estimates will be adjusted by mixed-effects regression models. Possible confounding or effect-modifying factors will be taken into account.

**Discussion:**

Assistance for the caregiver should be integrated into primary care services. In order to do so, incorporating standard, effective interventions with relevant outcome variables such as quality of life is necessary. Community care nurses are at a privileged position to develop interventions like the proposed one.

**Trial registration:**

This trial has been registered in ClinicalTrials.gov under code number NCT 01478295.

## Background

### Aging and dependency

Population aging constitutes one of the most relevant demographic phenomena of this century. The *World Population Ageing (2009)* report published by the United Nations in January 2010 shows that we are facing a general and unprecedented problem. According to their data and estimations, 11% of the population was >60 years old in 2009, and this figure is estimated to increase up to 22% in 2050. The report highlights that one of the fastest growing segments of the population will be the >80 year old, which will constitute 20% of the >60 year old group by 2050 [1].

The situation in Spain shows similar figures. The current aging index is 17%, 4% of people are >80 years old, and it is forecasted that 37% of the total population will be ≥60 years by 2049 [2].

This demographic phenomenon poses important economic and social health-related challenges. In the social realm, population aging influences migration tendencies as well as family composition and individual roles within it. In the health setting, morbidity related to the aging process and increases in the prevalence of chronic and degenerative diseases entails the emergence of dependency and a growing need for health care and services [3].

The European Council defines dependency as the state in which people, due to causes linked to the lack or loss of physical, psychological, or intellectual autonomy, are in need of assistance and/or significant help to carry out common activities of daily life, and particularly those related to personal care [4].

In Spain it is estimated that 9% of the total population present some handicap or limitation, of which one third shows severe dependency requiring help from someone to perform basic activities of daily living (BADL) [5]. The percentages of people >65 and >85 years old with any handicap are 32.2% and 63.3%, respectively. According to the *Encuesta Nacional de Salud 2011/2012*, 34.2% of the population ≥65 years in Spain state being in need of help for carrying out any BADL related to personal care, 37.5% for performing house work, and 36.2% do not consider themselves able to perform those related to mobility [6].

### Care of the dependent person

In situations of dependency, two care alternatives are usually present, formal and informal. Formal care has been defined as those services that are offered by a professional in a specialized manner and go further than the capabilities that people have to take care of themselves or others. It is usually provided by public institutions or hired from private companies by the family [7].

Informal care is that which stems from the family environment or social network of the dependent person. Its main features are its unpaid character, being carried out in the private realm, having a highly marked domestic content, and a mainly female profile. The person who assumes responsibility for the support and daily care of the dependent person is called the main caregiver [8].

There is interdependency between the formal and informal care sectors. In Spain, our model of home assistance for dependent people is based on the family as the care-giving unit, and health care is mainly provided by primary care. It is estimated that the family bears 88% of the total care time consumed by the dependent person [9]. The typical profile of the main caregiver is female (83%), of low educational level, who invests an average of 4 hours a day, without rest breaks, and receiving scarce institutional support [7]. According to the *Encuesta Nacional de Salud 2011/2012 *[6], 16.6% of men and 49.4% of women who live with handicapped people are responsible for providing care to them all by themselves.

### The main caregivers as a vulnerable group

Providing informal care is considered as an important stress source, even resulting in higher stress levels for caregivers than for the patients themselves [10].

In the last years, numerous articles have concluded that providing informal care constitutes an under-diagnosed, morbidity-generating circumstance [11-13]. The outcome of a prospective cohort study with a 4.5-year follow-up period indicated that married caregivers between 66 and 96 years old who took care of their couples had a 63% higher probability of dying from any cause within a follow-up period of 4 years compared to a control group of non-caregivers [12].

Studies of qualitative outcomes, such as the one by Teschendorf et al. [13], identify 4 categories of concerns and requests of cancer patients' caregivers: health care, strategies about how to deal with the role of a caregiver, emotional support, and social recognition.

### Interventions and strategies that take care of the main caregiver

In the last years, there is remarkable interest in evaluating the effect that interventions for the caregiver have on their health condition and quality of life, and published relevant systematic reviews are plentiful.

In a systematic review including 112 clinical trials whose objective was to evaluate the effect of different interventions on the burden of the main caregiver of demented patients, Goy et al. [14] conclude that complex interventions reduce the burden and increase the capacity to deal with it, especially when they are personalized, provided in the home, and oriented towards the specific needs of the caregiver-patient pair. The effect of personal assessment and support groups may vary depending on the trainer’s degree of skill, environment, frequency and duration of the contact, and employed teaching materials.

In another systematic review published by Parker et al. [15] to evaluate the effectiveness of psycho-educational interventions for caregivers of non-institutionalized patients with dementia, 12 of the 13 reviewed studies observed a significant association between such interventions and caregivers’ depression and overload. These authors conclude that interventions are more effective if there is a personalized program, active participation of the caregiver, and specific information is given. Those interventions that only provide mutual support, group work, and self-help materials do not seem to affect the burden.

In 2011, The Cochrane Collaboration published 2 systematic reviews [16,17] that evaluated the effectiveness of support interventions on the health of main caregivers of dependent people suffering from different pathologies.

Candy et al. [16] included 11 randomized controlled trials with 1,836 caregivers of terminal stage patients who received support interventions for the caring of the dependent person, emotional support, and/or tools to deal with it. The results suggest that emotional support interventions may help reduce the psychological unrest of the caregivers.

Legg et al. [17] included 8 clinical trials with a total of 1,007 caregivers of dependent patients suffering from stroke sequelae. They evaluated the effect of non-pharmacological interventions versus standard care. They classified the interventions into support and information, teaching of procedures, and psycho-educational. The results suggest that psycho-educational interventions before discharge of the patient have greater impact on the caregiver's burden.

However, it is difficult to draw conclusions about the effect that the interventions directed at the main caregiver have on their health and quality of life. The main limitations described in these reviews are related to the large number of different interventions evaluated, their complexity, and the difficulty of reproducing them [14-17].

Among the recommendations for future research, it is suggested that studies evaluate interventions in various contexts, implement methods to avoid losses to follow-up of the studied subjects, and evaluate different implementation strategies to determine the interventions’ acceptability, viability, efficacy, and cost-effectiveness [14].

Review studies show that quality of life, anxiety and depression levels, stress, and overload of the main caregiver are the outcome measurements used most frequently as main or secondary variables to evaluate the effectiveness of interventions aimed at the caregiver [16,17].

Several studies from our setting use EuroQol (EQ-5D) [18,19]. This tool has advantages in the setting of our study since it is a culturally-adapted instrument, highly validated in the Spanish population, with easy and rapid implementation, and which counts on standard scores obtained from the general population that can be used as reference values to compare against those obtained from studied patients and thus define the effect of the disease on the health-related quality of life (HRQL) [20,21].

### Structured care intervention in the area of primary care: intervention CuidaCare

The *Estrategia para el Abordaje de la Cronicidad en el Sistema Nacional de Salud *[22] considers the home as the ideal place for the care of dependent patients, since staying in one's own environment improves well-being and quality of life. It recognizes nurses, within a multidisciplinary team, as the professionals who lead and coordinate health care actions, both for the dependent person who requires home care and for their main caregiver. For the development of support and care programs aimed at chronic patients, the strategy indicates that they must be limited to not only developing informative activities and training on caregiving for the dependent person, but also include interventions for the caregivers themselves, addressing their problems and preventing pathological conditions and the risk of giving up.

In the Community of Madrid, the *Cartera de Servicios estandarizados de Atención Primaria *[23] considers the care of dependent patients within their scope of services, but does not explicitly consider the care of the main caregiver.

Normalization of nursing diagnostic process and usage of internationally recognized taxonomies (such as the NANDA-I for formulation of care problems, the NIC for intervention definition, and the NOC for result measurement) reduce variability in nursing clinical practice and facilitate normalization of caregiving, in addition to providing a tool that enables carrying out studies on the effectiveness of the interventions [24,25].

As a result, it seems adequate to put into practice community trials that allow for evaluating the effectiveness of complex, structured, and personalized nursing interventions.

The CuidaCare project proposes a community, pragmatic trial in primary care to evaluate the effectiveness of a complex, standard nursing intervention performed at the caregiver’s home that will measure relevant outcomes of the main caregivers.

### Hypothesis

A standard care intervention (intervention CuidaCare) in primary care is more effective than standard practice for improving the quality of life of old caregivers, as measured by the EQ-5D VAS, increasing the average pre- and post-intervention score change by ≥15 points between the intervention and control groups.

### Objectives

The objective of this study is to evaluate the effectiveness of a standard caregiving intervention (intervention CuidaCare) in primary care to improve the quality of life of main caregivers >65 years, as measured by the EQ-5D VAS during follow-up visits at 0, 6, and 12 months after the intervention.

#### Secondary objectives

• Describe the socio-demographic profile of the dependent patient and the main caregiver.

• Describe the degree of burden for the main caregivers, measured with the Zarit's test.

• Compare the effectiveness of the CuidaCare intervention against the standard nursing practice for improving the caregiver’s quality of life, measured with the EQ-5D Dimensions and the EQ-5D Index, at the end of the intervention and during follow-up visits at 6 and 12 months.

• Compare the effectiveness of the CuidaCare intervention with standard nursing practice in reducing caregiver burden, as measured by nursing outcome NOC Indicators and Zarit's test at the end of the intervention and during follow-up visits at 6 and 12 months.

• Analyze socio-demographic factors, characteristics of the dependent patient, caregiving attributes, and formal support that characterize the quality of life of the main caregiver.

## Methods/Design

### Study design

A community, controlled, multicentric clinical trial with randomized allocation by clusters and a 1-year follow-up period.

The intervention will be carried out by voluntary nurses with at least 3 years of experience in primary care, from 20 primary health care centers (PHCC) in the Community of Madrid (Spain).

The randomized unit will be the PHCCs (clusters). The analysis unit will be the caregiver (check-list cluster CONSORT in Additional file 1).

### Studied subjects

Subjects ≥65 years, identified by the nurse as the main caregiver of a patient included in the home consultation service of the *Cartera de Servicios estandarizados de Atención Primaria *[23] at the moment of inclusion in the study.

The person who assumes responsibility for the support and daily care of the dependent patient is termed the main caregiver [8].

1. Inclusion criteria:

• Age ≥65 years.

• Caregivers who have been carrying out this function for >1 month.

• Time employed as main caregiver is >6 months per year (even during non consecutive months).

• Not currently under another therapeutic intervention to ease caregiver tension.

• Able to follow the specific requirements of the trial.

• Willing to participate in the trial and provide written consent.

2. Exclusion criteria:

• Main caregivers of institutionalized patients.

### Sample size

Sample size has been calculated considering a relevant post-intervention average difference of 15 points between the intervention and control groups measured on the EQ-5D VAS, and a standard deviation of 25 (estimation obtained from Roset et al. [26]). This difference is equivalent to an effect size of 0.6.

Assuming an alpha error of 0.05 and a beta error of 20%, 44 caregivers are necessary for each group.

Since randomization is done by clusters, the sample size is adjusted in order to take into account the design effect. We have considered an intraclass correlation coefficient of 0.02 [27] and assumed an average cluster sample size of 15 caregivers. The design effect is 1.28. With these assumptions and expecting a 20% loss to follow-up after a 1-year period, the required sample size is 142 (71 caregivers per group).

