### Data collection method

Information will be collected via a clinical interview and data will be recorded in an electronic data collection notebook specifically designed for this trial. Variables will be collected during 4 visits: at the beginning of the trial, at the end of the intervention, and at 6 and 12 months after the intervention. The timing for the data collection is shown in Table 1.

**Table 1 T1:** Procedures to be followed and information to be recorded at each patient’s visit

	
Step 1	Recruitment of caregivers
	- Presentation/information about the trial
	- Invitation to participate
	- Checking inclusion/exclusion criteria
	- Signing of informed consent
	- Collection of sociodemographic variables (dependent patient and caregiver)
Step 2	Primary health care center randomization
Step 3	Base-line visit
	Collection of variables on:
	- Dependent Patient: degree of cognitive deterioration and dependency level.
	- Evaluation of formal support.
	- Caregiver: self-perceived quality of life, degree of burden, evaluation of anxiety/depression degree, Apgar family test, and nursing diagnosis.
Step 4	Intervention period (duration of 6 months)

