	**Control group**
	Standard care
Step 7	Follow-up (12 months after intervention). End of trial.
	Collection of variables on:
	- Dependent Patient: degree of cognitive deterioration and dependency level.
	- Evaluation of formal support.
	- Caregiver: self-perceived quality of life, degree of burden, evaluation of anxiety/depression degree, Apgar family test, and nursing diagnosis.

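### The design effect of 1.28 assumes 15 caregivers per centre, but 142 caregivers in 20 centres average 7.1; the mismatch is conservative, and the period that the 20% loss covers is unclear

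*Protocol article*

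**What the plan says.** The Sample size section starts from "a relevant post-intervention average difference of 15 points between the intervention and control groups measured on the EQ-5D VAS" and "a standard deviation of 25", which with a 5% alpha error and a 20% beta error gives 44 caregivers per group. It then takes an intraclass correlation of 0.02 and "assumed an average cluster sample size of 15 caregivers. The design effect is 1.28". Finally, "expecting a 20% loss to follow-up after a 1-year period", it concludes that "the required sample size is 142 (71 caregivers per group").

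The number of clusters is fixed elsewhere. The Study design section draws the nurses "from 20 primary health care centers (PHCC) in the Community of Madrid (Spain"), and Sequence generation allocates all 20 centres to the two arms. The abstract repeats both 20 and 142.

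On timing, Table 1 has a baseline visit, then an "Intervention period (duration of 6 months"), then visits at 0, 6 and 12 months after it, the last being "Follow-up (12 months after intervention). End of trial". The Analysis section compares change in EQ-5D VAS from before the intervention at all three of these visits.

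**The concern.** The average cluster size, the number of centres and the total cannot all be right. The design effect depends directly on cluster size, so 1.28 is not the value for the trial described. The sample size and the nominal 80% power inherit that mismatch, and a reader who takes the 20 centres at face value cannot recover the stated design effect.

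There is also a question about the loss allowance. Change from baseline at the last visit spans 6 months of intervention plus 12 months of follow-up, so 18 months. The allowance refers to one year. If the first 6 months were left out, fewer caregivers than planned would be available for the last analysis of the primary outcome.

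**Working it through.** **Inputs from the Sample size section:** difference 15, SD 25, alpha 0.05 (taken as two-sided, which reproduces the plan's 44), power 80%, ICC 0.02, cluster size 15, loss 20%. **From Study design and Sequence generation:** 20 centres.

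**1. Reproducing the plan's figure**
- Per group, unclustered: 2 × (1.96 + 0.8416)² × (25/15)² = 43.6, rounded up to 44.
- Design effect: 1 + (15 − 1) × 0.02 = 1.28.
- With loss: 44 × 1.28 / 0.80 = 70.4, rounded up to 71 per group, 142 in total.

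The plan's figure reproduces exactly. So 15 is the value that was used, and the arithmetic is sound. The fault is in the input.

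**2. Consistency of the inputs**
- 142 / 20 = 7.1 caregivers per centre.
- 20 × 15 = 300 caregivers.
- 142 / 15 = 9.5 centres.

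**3. Design effect and N for 20 centres**
- Equal centre sizes: 1 + (7.1 − 1) × 0.02 = 1.122. Then 44 × 1.122 / 0.80 = 61.7, so 62 per group, 124 in total.
- Unequal centre sizes, with coefficient of variation CV (the document gives none; 0.6 to 1.0 is an assumption): design effect = 1 + [(CV² + 1) × 7.1 − 1] × 0.02.
  - CV 0.6: 1 + (9.656 − 1) × 0.02 = 1.17; 44 × 1.173 / 0.80 = 64.5, so 65 per group (130).
  - CV 1.0: 1 + (14.2 − 1) × 0.02 = 1.26; 44 × 1.264 / 0.80 = 69.5, so 70 per group (140).

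**4. Power with 142 at the stated 20% loss** (equal centre sizes, design effect at the retained cluster size)
- Retained: 71 × 0.80 = 56.8 per group; 7.1 × 0.80 = 5.68 per centre.
- Design effect: 1 + 4.68 × 0.02 = 1.094.
- SE = 25 × √(2 × 1.094 / 56.8) = 4.91; 15 / 4.91 = 3.06.
- Power: 86% (normal); 82% (noncentral t, 20 − 2 = 18 df).
- Using the recruited cluster size of 7.1 instead changes the normal figure only to 85.5%.

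**5. Sensitivity for the last visit**
- Assumption: 20% is an annual rate and continues unchanged for 18 months. Loss = 1 − 0.80^1.5 = 28.4%.
- Retained: 71 × 0.716 = 50.8 per group, 5.08 per centre; design effect 1 + 4.08 × 0.02 = 1.082.
- SE = 25 × √(2 × 1.082 / 50.8) = 5.16; 15 / 5.16 = 2.91.
- Power: 83% (normal); 79% (t, 18 df).
- N by the plan's formula with cluster size 7.1: 44 × 1.122 / 0.716 = 69.0, so 69 per group (138), against 142 planned.

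**The case against.** The best defence is that the error does no harm. With 7.1 caregivers per centre, 142 exceeds what the plan's formula requires, and power at the stated loss stays above 80% under either reference distribution. This stands, and it is why N need not change.

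The second defence concerns the loss. The protocol calls the year after the intervention its follow-up period, so 20% after one year may mean cumulative loss by the end of that period, which is the last visit. The Discussion supports this by describing a high percentage over the trial because dependent patients are hospitalized or die. This also stands. A reader might infer that the plan overlooks six months of loss, but the text does not exclude the intervention months; it leaves the span unstated.

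A third point is that 1.12 assumes equal centres, whereas randomization is stratified by number of caregivers, which suggests that sizes vary. That is fair, and the restated design effect should carry a range.

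Finally, the normal approximation with a design effect is a standard method, and the document fixes no degrees of freedom. The 18-df figure is a refinement suited to 20 clusters. It does not contradict anything in the plan.

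**Conclusion.** The point holds as an inconsistency in a figure on which the sample size rests. The design effect of 1.28 belongs to centres of 15, and this trial has centres averaging 7.1. The matching value is about 1.12 with equal sizes (about 1.17 to 1.26 if the coefficient of variation is 0.6 to 1.0, an assumption), and the required total at 20% loss is 124 rather than 142.

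It does not show that the trial is underpowered. A reader might infer that centres would recruit 15 each and that recruitment would close after about ten of them, with a loss of power. The document does not support this: it sets no target of 15 per centre, it fixes 20 centres, and all 20 are randomized after the eligible caregivers have been chosen.

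The loss period is an ambiguity. The 28% loss and the 79% to 83% power at the last visit rest on a constant annual rate that the document does not state. They are sensitivity figures and should not replace the stated 20%.

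**What to change.** Rewrite the Sample size paragraph and keep N = 142:
- Base it on 20 centres averaging about 7 caregivers.
- Give the design effect as about 1.12 at ICC 0.02, with a range for unequal centre sizes and the assumed coefficient of variation.
- Restate power at 20% loss: about 86% by normal approximation, about 82% with a t reference on 18 df, and say which is used.
- State whether the 20% covers the full 18 months from baseline to the last primary visit or one year only. If one year only, add the expected loss over 18 months and the power at that visit.

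The cost is the rewording of one paragraph. No caregivers, centres or visits are added. At the stated 20% loss the restated power is higher than the nominal 80%. Only if the loss is annual and continuing, and the t reference is used, does it fall slightly below that level at the last visit.
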